### **6.3 Data collection at postoperative hospitalization**

Since POAF is influenced by a great deal of aspects, data collection shall be comprehensive. Both intraoperative characteristics and postoperative data will be collected at this period:

- 1) Operation time, cardiopulmonary time, cross clamp time, number of total/artery/venous grafts.
- 2) Postoperative laboratory tests and examinations: blood, biochemistry, coagulation, biomarker, transthoracic echocardiography and 12-lead-ECG at discharge.
- 3) Intensive care unit stay, length of hospitalization, postoperative costs, blood transfusion, secondary operation, complications such as stroke, acute kidney injury and postoperative myocardial infarction.

- 4) The prescription of medications in postoperative hospitalization and at discharge.
- 5) The continuous ECG monitoring device will be removed from participants at discharge and handed to function test department for data exportation and analysis.

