## **1.4 Benefit /risk and ethical assessment**

The intervention group will receive additional partial cardiac denervation procedure, namely cutting off the LOM and resecting the fat pad along the Waterston groove. Potential risks are as follows: extending operation time, increasing intraoperative blood loss and postoperative arrhythmias. The related technique has been applied in surgical treatment of AF and proved to be safe and feasible. The surgery will remove only part of the CANS and will not affect the patient's normal sinus rhythm. All the participants can contact the the study physician who will help them to get the right medical treatment, if any suspected arrhythmias-related adverse events emerge after surgery. The study will be approved by the Institutional Review Board of Fuwai Hospital.

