### **2.2.2 Economic assessments**

- 6) Length of hospitalization;
- 7) All costs during hospitalization;
- 8) All costs after the surgery;

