**Figure 1. The study flow Chart.**

### **3.4 Partial cardiac denervation procedure**

In the intervention group, participant will undergo partial cardiac denervation through cutting off the LOM and resecting the fat pad along the Waterston groove. Specifically, during the on-pump CABG, the heart will be pulled to the right to expose the LOM between the left atrial appendage and the left pulmonary veins under extracorporeal circulation, and the LOM will be cut off by electrotome. Then, the fat pad along the Waterston groove will be exposed between the right pulmonary veins and right atrium and excised completely to the surface of myocardium, with the upper edge extending beyond the opening of the right upper pulmonary vein and the lower edge to the inferior vena cava. For off-pump CABG, we will cut off the LOM in the same way mentioned above. Then if the patient's heart is well tolerated and hemodynamics is stable, a fixator can be used to fix the heart when resecting the fat pad along the Waterston groove. Otherwise, cardiac denervation will be performed after CABG is completed. The estimated additional surgery time is 5 minutes. In order to achieve a satisfactory efficacy, a thorough cardiac denervation to myocardium surface will be emphasized. In addition, the existence of ganglia will be further proved through histologic analysis using the fat pad samples collected from 10 pairs of patients with or without POAF, respectively.

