### **4.2 Baseline comparability of randomized groups**

Demographic and clinical characteristics of patients at baseline will be presented by randomised group. Number of subjects, mean, standard deviation, median, interquartile range (IQR), minimum, and maximum will be used for description of continuous variables. Continuous variables will be tested by Student's t test if normally distributed; otherwise, by the Mann-Whitney U test. Counts and percentages will be used to summarize the categorical variables. Chi-squared test or Fisher's exact test will be applied for categorical variables, as appropriate.

Intraoperative data such as number of grafts, % off pump, % saphenous vein/radial artery, duration of operation will also be presented.

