## **8. Statistical test for secondary endpoints**

### **8.1 Statistical analysis method**

Secondary outcomes including safety and economics will also be analyzed according to approach mentioned in 4.2. Unless otherwise stated, statistical significance level is set to 0.05 (2-sided).

For clinical concerns, the incidence of epicardial effusion within 30 days after discharge and arrhythmias other than AF within 30 days after discharge will be analysed as delayed epicardial effusion and critical arrhythmias, respectively. Delayed epicardial effusion was defined as new-onset epicardial effusion (moderate or more) within 30 days after discharge. Critical arrhythmias other than AF was defined as arrhythmias requiring immediate clinical intervention, such as complete atrioventricular block.

Since POAF happens after surgery and has a effect on postoperative clinical events, we think the analysis of all cost during hospitalization may not be appropriate. Only postoperative cost for each patient will be included in the final analysis. Similarly, only postoperative length of hospitalization will be included in the final analysis.

Although the follow-up visit of 30 days is relative short, we intend to compare the MACCE outcome between the 2 groups in the final manuscript.

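### The cost comparison starts after surgery, so on the plain reading it counts savings from less POAF but omits any added operating-room cost of the denervation, while total hospitalisation cost stays listed but unanalysed

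*Supplement*

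**What the plan says.** Section 2.2.2 of the current SAP lists two cost outcomes, "All costs during hospitalization" and "All costs after the surgery". Section 2.2.2 of protocol version 2.0 lists the same two.

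SAP 8.1 then narrows this. It notes that POAF happens after surgery, states that "we think the analysis of all cost during hospitalization may not be appropriate", and concludes: "Only postoperative cost for each patient will be included in the final analysis". Economic outcomes are otherwise sent to the approach of SAP 4.2: "Continuous variables will be tested by Student's t test if normally distributed; otherwise, by the Mann-Whitney U test".

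On data capture, protocol 6.3 names "Intensive care unit stay, length of hospitalization, postoperative costs, blood transfusion, secondary operation". The protocol's SPIRIT schedule has separate columns for surgery and for the postoperative hospital stay, and its only cost row is marked in the second.

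On the intervention, SAP 3.4 places the denervation within the CABG operation and says: "The estimated additional surgery time is 5 minutes". SAP 1.4 adds: "Potential risks are as follows: extending operation time, increasing intraoperative blood loss and postoperative arrhythmias".

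**The concern.** The reason in 8.1 concerns where the outcome occurs. For a cost comparison it also matters where the intervention occurs, and here that is the operating room. A window that opens after surgery takes in what denervation may save (treatment of POAF, longer stay) and leaves out what it may add (operating time, intraoperative blood products, conversion to on-pump surgery). The omission therefore runs in one direction.

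At stake is a secondary economic statement. If the report says that denervation lowers cost, readers will take that as net of doing the procedure, and the planned figure would not be net of it. In addition, an outcome that both current documents list would go unreported, and 2.2.2 does not tell the reader so.

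**Working it through.** **What can be reproduced.** The documents give no cost, standard deviation or expected cost difference, so there is no cost figure to reproduce. The planning inputs used below are the 23% control rate and the 50% relative reduction in SAP 3.5, giving 0.23 × 0.5 = 0.115 in the intervention arm and an absolute reduction of 0.23 − 0.115 = 0.115. (The stated 408 participants are reproduced with 12% in the intervention arm and a continuity correction. On that rounding the reduction would be 0.23 − 0.12 = 0.11. Nothing below depends on the choice.)

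**Step 1: which costs can allocation change?**

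| Period | Can allocation change cost? | Does the reason in 8.1 cover dropping it? | In the planned analysis? |
|---|---|---|---|
| Before surgery | No: the surgeon learns the group only after general anaesthesia, and patients are blinded (SAP 3.6) | Yes | No |
| During surgery | Yes: denervation is delivered here (SAP 3.4) | No | No, on the plain reading |
| After surgery | Yes, through POAF and complications | Not applicable | Yes |

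**Step 2: is operating-room cost really excluded?** Neither document defines when postoperative cost starts. The SPIRIT schedule supports the plain reading. It marks conversion to on-pump under surgery and transfusion under both surgery and the postoperative stay, but cost only under the postoperative stay.

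**Step 3: size and direction.** Let C be the mean added intraoperative cost per denervation patient and D the mean difference in postoperative cost (denervation minus control).

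- Planned analysis estimates: D
- Cost from operating-room entry estimates: C + D
- Gap: C, whatever the value of D

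When C > 0, the planned figure favours denervation by C.

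**Step 4: when would the sign change?** Suppose denervation alters postoperative cost only by preventing POAF, and each case avoided saves S. Then D = −0.115 × S, and the operation-inclusive difference is C − 0.115 × S. This is positive only if C > 0.115 × S, that is, if S < C / 0.115 ≈ 8.7 × C. With a reduction of 0.11, the factor is 1 / 0.11 ≈ 9.1.

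**Step 5: illustration under an assumption.** The documents do not say what POAF adds to cost. Assume 10% to 50% of a POAF-free patient's postoperative cost:

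- 0.115 × 0.10 = 1.15%
- 0.115 × 0.50 = 5.75%

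On this assumption C would have to exceed about 1.2% to 5.8% of that cost before the sign changed. This bounds the saving only. The documents give no value for C, so they cannot show whether the threshold is reached.

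**Step 6: listed against analysed.** Total hospitalisation cost is item 7 in SAP 2.2.2 and in protocol 2.2.2. SAP 8.1 excludes it from the final analysis. Protocol 6.3 and the SPIRIT schedule name only postoperative cost for collection. The lists do not agree.

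**The case against.** **The narrowing is open.** A reader might infer a concealed change of endpoint. The documents do not support that. SAP 8.1 names the outcome it drops and gives a reason, the SAP's summary of changes repeats it, and the retained outcome was already item 8 of the same list. It also matches what protocol 6.3 and the SPIRIT schedule collect. What remains of this part is one list item left unreconciled.

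**The plan is not blind to intraoperative resource use.** Transfusion and conversion to on-pump are compared between arms as safety outcomes. Operation duration and the proportion off-pump are presented under SAP 4.2, although operation time is not itself a listed safety outcome. A rise in resource use would be partly visible, but not in money and not inside the cost result.

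**The added cost is probably small.** About 5 minutes, an electrotome, and a fixator in some off-pump cases do not suggest a large C. This stands, although a conversion or an intraoperative transfusion would add to it in the patients affected.

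**The cut-off is inferred.** This is true. It is an argument for defining the window, and it does not remove the gap on the natural reading.

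**The choice of test is a side issue.** A Mann-Whitney test, the likely route if costs are skewed, does not compare mean costs. But 8.1 refers economic outcomes to 4.2, which includes means and standard deviations among its descriptive statistics, so arm means can be expected. What is missing is a stated difference in means with an interval.

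**Conclusion.** The point holds in a limited form. The reason given in 8.1 covers preoperative cost and not operating-room cost. On the plain reading of an undefined window, the cost comparison favours denervation by C, the added intraoperative cost per patient. C is unquantified in the documents and plausibly small.

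A reader might go further and infer that the trial would report a saving where total cost is equal or higher. That is possible if C exceeds 0.115 × S under the planned rates, but the documents give neither C nor S, so it is not shown.

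In addition, total hospitalisation cost is listed in SAP 2.2.2 and protocol 2.2.2 but not analysed. All of this concerns a secondary economic outcome and leaves the conclusion on POAF untouched.

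**What to change.** In SAP 8.1:

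- Define the cost window. Analyse cost from operating-room entry to discharge, or the already listed total hospitalisation cost, alongside postoperative cost. Preoperative cost should balance in expectation, so either choice includes C. The total brings in preoperative variation as well.
- Report the difference in arithmetic mean cost with a 95% CI, for example by bootstrap.
- State that any claim of lower cost will rest on the operation-inclusive figure.

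Then make SAP 2.2.2 and protocol 2.2.2 agree with 8.1, and add the required cost items to protocol 6.3 and the SPIRIT schedule.

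The price is some extra extraction of billing data, since only postoperative cost is now named for collection, and possibly a wider interval. No change to the sample size or the primary analysis is needed. If C is negligible, the two cost figures shown side by side will demonstrate it.

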## **8.2 Missing data**

Since the secondary endpoints are events occurring either in participant's hospitalization or a relatively short follow-up visit (30 days after discharge), missing data shall not be expected. Any missing data won't be imputed.

## **9. Statistical analysis software**

Statistical analyses will be performed by using R 4.0.2 (R Core Team, Vienna, Austria) and Stata 15.0 (StataCorp, College Station, TX, USA).

## **10. Interim analysis**

No interim analysis for this study.

## **Summary of changes of the Statistical Analysis Plan from version 1.0 to version**

### **3.0**

For clinical concerns, the incidence of epicardial effusion within 30 days after discharge and arrhythmias other than AF within 30 days after discharge will be analysed as delayed epicardial effusion and critical arrhythmias, respectively. Delayed epicardial effusion was defined as new-onset epicardial effusion (moderate or more) within 30 days after discharge. Critical arrhythmias other than AF was defined as arrhythmias requiring immediate clinical intervention, such as complete atrioventricular block.

Since POAF happens after surgery and has a effect on postoperative clinical events, we think the analysis of all cost during hospitalization may not be appropriate. Only postoperative cost for each patient will be included in the final analysis. Similarly, only postoperative length of hospitalization will be included in the final analysis.

Although the follow-up visit of 30 days is relative short, we intend to compare the MACCE outcome between the 2 groups in the final manuscript.
